### Esketamine treatment (T1A-F)

The inpatient treatment arm receives continuous intravenous esketamine infusions for 6 consecutive days during a hospital admission (T1A). The outpatient arm will receive 6 esketamine infusions: one 6-hour infusion every 2 weeks for 3 months, in a day-care setting (T1A-F). Esketamine will be administered by a trained nurse under supervision of a pain specialist.

### Follow-up measurement T2A-F

All patients will be called every 2 weeks (T2A-F). They will be asked for their NRS pain score and if they have experienced any side effects of the esketamine treatment. In addition, the questions of the Global Perceived Effect will be asked [20].

### Follow-up measurement T3

At the 3-months follow-up measurement (T3), the same set of measurements conducted at baseline will be repeated. Only for the QST, a limited protocol will be performed to decrease patient burden: only temporal summation, pressure algometry and conditioned pain modulation will be assessed to provide information on pain processing. Our research group prefers to conduct only specific subsets that are suggested to be effected by esketamine treatments and give information on pain processing. The features temporal summation, pressure algometry and conditioned pain modulation might predict treatment outcome of pain relief by esketamine treatment [38–40]. Bosma et al. showed that neuropathic pain patients who have enhanced temporal summation of pain benefit from treatment with ketamine [38]. With regard to pressure algometry, Kirkpatrick et al. reported that clinical outcomes correlated with improvement in pain thresholds by pressure algometry in CRPS patients [40]. They suggested that pain thresholds by pressure algometry are a valid method to measure pain in CRPS as well as to measure clinical outcome after treatment with ketamine [40]. Furthermore, Niesters et al. reported enhanced conditioned pain modulation responses in neuropathic pain after ketamine infusion [39]. The observed treatment effects in neuropathic pain patients suggest a role for conditioned pain modulation engagement in analgesic efficacy of ketamine treatment [39]*.*

### Follow-up measurement T4

At 6-months, patients will be called for their last follow-up measurement (T4). They will be asked for their NRS pain score, the Global Perceived Effect [20] and the EQ-5D-5L [21]. After the end of the study, all participants will continue to receive standard follow up medical care for their CRPS.

### Sample size

Three months after the inpatient treatment the investigators expect a reduction of the average NRS pain score for pain from 8.0/10 to 6.0/10 (SD 1.5) and for the outpatient group from 8.0/10 to 6.0/10 (SD 1.5). These expectations are derived from a retrospective study of the inpatient continuous esketamine treatment for CRPS patients at the Center for Pain Medicine [13]. If there is truly no difference between the continuous esketamine treatment and the intermittent outpatient esketamine treatment, then 56 patients are required to be 80% sure that the lower limit of a 95% confidence interval will be above the non-inferiority limit of − 1.0. We aim to include 60 CRPS patients that will be randomized between outpatient and inpatient esketamine treatment.

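### The sidedness of the 95% confidence interval in the sample size is not stated: 56 patients with 80% power matches a one-sided 95% limit, while an ordinary two-sided 95% interval gives about 70% unadjusted

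*Protocol article*

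**What the plan says.** The Sample size section of the protocol article expects mean NRS pain to fall from 8.0 to 6.0 in each arm, with SD 1.5 in each. Its power statement assumes that the two regimens do not truly differ and sets the margin at −1.0: "56 patients are required to be 80% sure that the lower limit of a 95% confidence interval will be above the non-inferiority limit of" that value. The recruitment target is given separately: "We aim to include 60 CRPS patients that will be randomized between outpatient and inpatient esketamine treatment". The Recruitment, allocation and blinding section gives 1:1 allocation.

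The Statistical methods section plans linear regression for continuous outcomes, accounting for the stratification factor (earlier esketamine treatment), by intention to treat. It gives no alpha, no interval level and no sidedness for the non-inferiority comparison. The Sample size sentence is therefore the only place in the article where the non-inferiority rule appears.

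**The concern.** The sentence ties three things together: a number of patients, a power and an interval. When a 95% confidence interval is named without qualification, most readers take it as two-sided, and its lower limit then tests non-inferiority at one-sided 0.025. The number of patients given does not go with that level.

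The interval level decides the primary claim. If the 90% interval lies above −1.0 but the 95% interval does not, the two readings give opposite conclusions. A reader who takes the interval as two-sided will overestimate the power. If a one-sided 5% test was meant, the same reader will believe that the chance of wrongly declaring non-inferiority at the margin is 2.5%, when it is 5%. The article also says that the statistician is not blinded during analysis, which is a further reason to have the rule in plain words beforehand.

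**Working it through.** **Inputs**, all from the article: SD 1.5 in both arms; margin 1.0; true difference 0; power 80% (z = 0.8416); allocation 1:1. No baseline correlation, dropout rate or other variance adjustment is stated. The comparison is therefore taken as unadjusted.

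**Formula for patients per arm** (normal approximation): n = 2 × SD² × (z_alpha + 0.8416)² / margin², with 2 × 1.5² / 1.0² = 4.5.

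**Reproducing the plan's figure.** One-sided alpha 0.05 (one-sided 95% limit, the same as the lower limit of a two-sided 90% interval): n = 4.5 × (1.6449 + 0.8416)² = 27.8, so 28 per arm and **56 in total**. This is the stated figure.

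**The ordinary reading.** One-sided alpha 0.025 (lower limit of a two-sided 95% interval): n = 4.5 × (1.9600 + 0.8416)² = 35.3, so 36 per arm and **72 in total**, which is 16 more than stated.

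**Power at the stated and planned sizes.** Power = Φ(margin/SE − z_alpha), with SE = 1.5 × √(2/n).
- 56 patients (28 per arm): SE = 0.4009 and margin/SE = 2.494.
- 60 patients (30 per arm): SE = 0.3873 and margin/SE = 2.582.

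The noncentral t distribution gives a check on each value.

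| Interval | Total N | Power, normal | Power, t |
|---|---|---|---|
| One-sided 95% (two-sided 90%) | 56 | 80.2% | 79.3% |
| One-sided 95% (two-sided 90%) | 60 | 82.6% | 81.8% |
| Two-sided 95% | 56 | 70.3% | 68.8% |
| Two-sided 95% | 60 | 73.3% | 71.9% |

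With the t distribution, 80% power needs 58 patients at one-sided 0.05 and 74 at one-sided 0.025. The choice between normal and t therefore does not explain the gap.

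**How often the two rules disagree.** At 60 patients and no true difference, the 90% interval succeeds where the 95% interval fails in 82.6% − 73.3% = 9.3% of trials (normal approximation, unadjusted, all 60 with a 3-month score).

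**Another way to reach 56.** A two-sided 95% interval would give 80% power at 56 if the variance were multiplied by 56 / (4 × 1.5² × (1.9600 + 0.8416)²) = 56 / 70.64 = 0.793. That means an SD of 1.5 × √0.793 = 1.34, or adjustment for baseline NRS with a correlation of √(1 − 0.793), about 0.46. The article states neither.

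**The case against.** The strongest reply is that there is no arithmetic error. The rule concerns one limit only, "the lower limit of a 95% confidence interval will be above the non-inferiority limit of" −1.0, and the words two-sided never appear. Read as a one-sided 95% limit, 56 is exactly right, and that exact match makes this the likely intent. This stands. A reader might infer that the sample size was miscalculated, but the article does not support that. What remains is that the sentence leaves out the word that makes it true, and its ordinary reading makes it false.

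A second reply is that the planned regression could recover power. A reader might infer that the trial will in fact run at about 70% power. That goes too far, because 70% is an unadjusted figure. If baseline NRS were in the model, a two-sided 95% interval would need 66, 54 or 38 patients for assumed baseline-to-3-month correlations of 0.3, 0.5 or 0.7. But the article gives no correlation, and the only factor its Statistical methods section names is earlier esketamine treatment. Adjustment therefore cannot be credited as the basis of the stated 80%.

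A third reply is that the article condenses a full protocol (version 3, February 2022) that is not shown, and that protocol or an analysis plan may fix alpha and sidedness. This also stands. A reader might infer that the analyst is free to choose the interval after seeing the data; the article alone cannot show that. Such a document would show which rule was meant. It would not make the published sentence correct on its ordinary reading.

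**Conclusion.** The point holds as an unresolved mismatch between the wording and the number. With the article's own inputs and an unadjusted comparison, 56 patients and 80% power belong to a one-sided 95% limit. Under a two-sided 95% interval, power falls short of 80% by about 10 percentage points at 56 and about 7 at 60, or by 16 patients.

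This rests on SD 1.5 in both arms, no true difference, equal arms, no covariate adjustment, and every counted patient having a 3-month score. It does not show that the sample size is wrong, or that the final analysis will have 70% power. It shows that the reader cannot tell from the article which of two decision rules governs the primary claim, and that the stated power belongs to only one of them.

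**What to change.** Before any data are analysed, replace the sentence in the Sample size section with one of the following, and repeat the same interval in the Statistical methods section and the analysis plan.

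1. State that non-inferiority is judged on the lower limit of the one-sided 95% confidence interval (equivalently the two-sided 90% interval), with one-sided alpha 0.05. Keep 56 and 80%, and use that interval for the primary analysis.
2. State that the interval is two-sided 95% (one-sided alpha 0.025), and restate unadjusted power as about 70% at 56 and 73% at 60.

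If the full protocol already fixes the rule, the choice is made and the article's sentence should be brought into line with it. The cost is one sentence and a less favourable published figure: a 5% one-sided error rate under the first option, or a lower power under the second. No extra patients are proposed, and nothing else in the design changes.

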### Statistical methods

Descriptive statistics are used to determine the frequency distributions of demographic variables, and to describe measures of central tendency and of dispersion, dependent on the shape of their distribution. The Shapiro-Wilk test is used to analyze whether or not continuous parameters are normally distributed. The effects of the treatment on the different study parameters will be evaluated with regression models to account for the stratification factor, received esketamine treatment in the past, in the randomization process. Continuous outcomes will be analyzed with a linear regression model, where the residuals will be evaluated for normality. In case of a violation of the assumption, (logarithmic) transformations will be applied. Count outcomes will be analyzed with Poisson regression models and binary outcomes with logistic regression models. For repeated measurements mixed effects, models will be used to account for correlations from measurements within the same patient. No correction of the rejection zone will be made for multiple comparisons, because of the more explorative nature of the analyses of the secondary and other parameters. All analyses will be conducted in accordance with the intention-to-treat principle. Data will be analyzed using the latest version of SPSS and R.

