### Outcomes

The primary outcome parameter is perceived pain intensity measured by Numerical Rating Scale (NRS) at T3 and will be compared to the baseline NRS pain scores (T0). The NRS ranges from 0 (no pain) to 10 (worst pain imaginable). Both the current NRS pain score and the average NRS pain score of the last 24 hours will be asked during all study visits.

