### Economic evaluation

An economic evaluation will be performed with a health care perspective according to the Dutch national guidelines for economic evaluation [41]. The time horizon of the economic evaluation will correspond to the trial follow-up of 6 months. A cost-effectiveness and a cost-utility analysis will be conducted. Incremental cost-effectiveness ratios will be calculated by dividing the difference in mean costs by the difference in mean effects of the intermittent and continuous esketamine treatment groups. For the effects, the parameters pain intensity measured by the NRS pain score and the Global Perceived Effect [20] will be used. Cost-utility will be based on the EQ-5D-5L [21] and expressed in costs per quality-adjusted life years (QALYs). Bootstrapping techniques will be used to estimate statistical uncertainty and the multiple imputation by chained equation approach will be used for missing data in the economic evaluation.

Healthcare utilization includes hospitalizations, outpatient visits, procedures, diagnostic tests and the prescription of pain medication. These data will be gathered during the prospective study. The costs of healthcare utilization will be valued using Dutch standard costs and prices provided by professional organizations such as the National Health Care Institute if standard costs are not available. The costs of medication will be valued using the prices of the Royal Dutch Society of Pharmacy.

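### The primary regression as described adjusts for prior esketamine only, leaving the collected T0 NRS unused as a covariate and the primary score and contrast unwritten

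*Protocol article*

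**What the plan says.** All references are to the Methods of the protocol article.

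- **Statistical methods.** Treatment effects, for every outcome studied, "will be evaluated with regression models to account for the stratification factor, received esketamine treatment in the past, in the randomization process". Linear regression is used for continuous outcomes, with transformation (a logarithm is suggested) if the residuals are not normal. Repeated measurements get mixed models. The section does not say which model carries the primary test, and it does not repeat the non-inferiority rule.
- **Outcomes.** The primary parameter is "perceived pain intensity measured by Numerical Rating Scale (NRS) at T3 and will be compared to the baseline NRS pain scores (T0"). The form of that comparison is not given. Two scores are collected: "Both the current NRS pain score and the average NRS pain score of the last 24 hours will be asked during all study visits". Neither is expressly named as primary.
- **Sample size.** For the inpatient arm the investigators "expect a reduction of the average NRS pain score for pain from 8.0/10 to 6.0/10 (SD 1.5"), and the same "for the outpatient group from 8.0/10 to 6.0/10 (SD 1.5"). If the arms truly do not differ, "then 56 patients are required to be 80% sure" that the lower 95% confidence limit lies above -1.0. The target is 60 patients. The section does not say whether 1.5 is the SD of the T3 score or of the change, and it does not write out the subtraction to which -1.0 applies.

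**The concern.** Pain at baseline usually predicts pain at follow-up. A regression of T3 NRS that leaves T0 NRS out carries avoidable residual variance, and with about 30 patients per arm a chance imbalance at baseline passes into the estimate. Comparing T3 with T0 could instead mean a change score. That uses T0, but with a fixed coefficient of one, which is inefficient when the correlation is modest.

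Three smaller points concern the same primary test. The article does not say outright which NRS score is analysed. It does not write the contrast to which -1.0 belongs. It allows a transformation, yet a limit of one NRS point has no meaning on a log scale, and the logarithm is undefined for a score of 0.

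At stake are precision that costs nothing to obtain and a primary test that can be read in only one way.

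**Working it through.** **Inputs from the article:** limit 1.0 NRS point in size, SD 1.5, true difference 0, power 80%, 1:1 allocation, 56 patients required, 60 planned (30 per arm).

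**Assumed:** the T0-T3 correlation r, which the article does not give. The range is 0.3 to 0.7, with 0.2 as a low case.

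**Step 1: the article's own figure.** With the normal approximation, n per arm = 2 × SD² × (z_α + z_0.80)² / 1.0².
- One-sided 5%: 2 × 2.25 × (1.645 + 0.842)² = 27.8, so 28 per arm and 56 in total. This matches.
- One-sided 2.5%: 2 × 2.25 × (1.960 + 0.842)² = 35.3, so 36 per arm and 72 in total. This does not match.

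The 56 is therefore a comparison of two means at one-sided 5%, with no baseline covariate. Whether the 95% interval is meant as one-sided or two-sided is a separate question, so both levels are shown below.

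**Step 2: residual SD if 1.5 is the SD at T3.**
- Raw T3 score: 1.5.
- T0 as covariate: 1.5 × √(1 − r²).
- Change score, taking the T0 SD as 1.5 too: 1.5 × √(2(1 − r)).

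**Step 3: power with 30 per arm.** Noncentral t, noncentrality 1.0 / (SD × √(2/30)). Raw T3 gives 82% at one-sided 5% and 72% at one-sided 2.5%.

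| r | SD, T0 as covariate | Power 5% / 2.5% | SD, change score | Power 5% / 2.5% |
|---|---|---|---|---|
| 0.3 | 1.43 | 85% / 76% | 1.77 | 70% / 57% |
| 0.5 | 1.30 | 90% / 83% | 1.50 | 82% / 72% |
| 0.7 | 1.07 | 97% / 94% | 1.16 | 95% / 91% |

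At r = 0.2 the covariate gives SD 1.47 and 83% at one-sided 5%. The change score is worse than raw T3 at 0.3, equal to it at 0.5 and better at 0.7. The covariate model is at least as precise as both at every value tried.

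**Step 4: the other reading, 1.5 as the SD of change.** With equal SDs at T0 and T3, the adjusted SD is 1.5 × √((1 + r)/2) = 1.21, 1.30 and 1.38 at r = 0.3, 0.5 and 0.7. Each is below 1.5, so adjustment still gains on the change score.

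**Step 5: interval width.** The two-sided 95% half-width is about 1.96 × SD × √(2/30). It is 0.76 for raw T3, and 0.72, 0.66 and 0.54 with T0 as covariate at r = 0.3, 0.5 and 0.7.

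**Step 6: direction.** Lower NRS is better. A rule that the lower limit must exceed -1.0 is coherent for the outpatient minus inpatient reduction, or for inpatient minus outpatient T3 NRS. With T0 in the model these two contrasts give the same estimate.

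**The case against.** The statistical methods section is one general paragraph covering every study parameter in a condensed article. It does not say that prior esketamine is the only covariate, and it does not exclude T0 NRS. A fuller covariate list may stand in the analysis plan. This is fair, and it makes the point a recommendation to complete the model rather than a demonstrated error. What remains is that the article does name its adjustment factor, and T0 NRS is not among those named.

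The size also rests on assumptions: no correlation is given, and neither is an SD at T0. Selecting patients with severe pain could narrow the baseline spread and lower the correlation. With r = 0.2 the gain is about one percentage point. The direction of the gain does not depend on these assumptions; its size does.

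A reader might infer more than the article supports:

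- *That the rule would pass a worse outpatient arm.* This needs an outpatient minus inpatient difference in T3 pain, which the article never states. The sample size section speaks of a reduction, which gives the limit a coherent direction.
- *That the primary score is wholly open, so the better of two could be reported and the error rate inflated.* The sample size section's reference to an average NRS score points towards the 24-hour score, although it could also mean a group mean. Nothing suggests that the better result would be chosen.
- *That patients without a T3 value are dropped.* The article says that "the multiple imputation by chained equation approach will be used for missing data in the economic evaluation", but it also plans mixed models for repeated measurements and intention-to-treat for all analyses. How missing primary data are handled is ordinary content of an analysis plan.
- *That a change score always loses power.* It loses against raw T3 only below a correlation of 0.5, given equal SDs at T0 and T3.

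**Conclusion.** The point holds in a limited form. The primary analysis as described does not use T0 NRS as a covariate, and using it is at least as precise as a raw T3 score or a change score at every correlation tried, under either reading of the SD. With 60 patients and 1.5 as the SD at T3, the gain over raw T3 at one-sided 5% is 3, 8 or 15 percentage points at assumed correlations of 0.3, 0.5 and 0.7 (82% to 85%, 90% or 97%). At one-sided 2.5% it is 4, 11 or 22 points (72% to 76%, 83% or 94%). It is small if the correlation is low.

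The primary score, the contrast and the scale each need a short clarification. The article's wording already points to a sensible answer on score and direction, so these are matters of wording and not evidence that the test is wrong.

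**What to change.** State one primary model, in words such as: *The primary analysis is a linear regression of NRS at T3, on the untransformed 0-10 scale, on treatment arm, prior esketamine treatment and the same NRS score at T0. The estimate is the adjusted mean difference, inpatient minus outpatient, so that negative values mean more pain in the outpatient arm. Non-inferiority is concluded if the lower confidence limit is above -1.0.*

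The same sentence should name the primary score. The 24-hour average fits the sample size wording best, but either can serve if it is named before analysis; the other becomes secondary. Exempt the primary outcome from the transformation rule so that the limit stays in NRS points.

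The cost is a sentence in the analysis plan and one degree of freedom. T0 NRS is already scheduled for every patient, so no visit, measurement or patient is added.

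### The transformation rule for non-normal residuals does not exempt the primary NRS analysis, whose non-inferiority limit of −1.0 exists only in raw NRS points

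*Protocol article*

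**What the plan says.** Three parts of the protocol article bear on this.

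- **Outcomes.** The endpoint is set out as follows: "The primary outcome parameter is perceived pain intensity measured by Numerical Rating Scale (NRS) at T3 and will be compared to the baseline NRS pain" rating at T0. On the scale: "The NRS ranges from 0 (no pain) to 10 (worst pain imaginable"). Zero is therefore an allowed value.
- **Sample size.** The assumption for each arm is "a reduction of the average NRS pain score for pain from 8.0/10 to 6.0/10 (SD 1.5"). Success requires this: "lower limit of a 95% confidence interval will be above the non-inferiority limit", which is set at −1.0. Means, SD and limit are all in NRS points.
- **Statistical methods.** Continuous outcomes get a linear regression that accounts for the stratification factor (previous esketamine treatment), and the residuals are checked for normality. Then: "In case of a violation of the assumption, (logarithmic) transformations will be applied". The sentence is worded for continuous outcomes in general. It does not set the primary outcome apart, restate the limit on another scale, or say how zero or negative values would be handled.

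The section on recruitment, allocation and blinding adds that the statistician is not blinded during data collection or analysis.

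**The concern.** The trial's conclusion rests on one comparison of one confidence limit with one number, and that number is a difference in NRS points. The transformation rule is an instruction, and as worded it reaches the primary analysis. If it is followed there, the model estimates something else: with a logarithm, a ratio of geometric means. The protocol gives no limit for that quantity.

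The team would then have three options: set the rule aside, set a new margin, or choose a way back to raw points. Each would be decided after the residuals, and therefore the outcome data, had been seen by an unblinded analyst. A non-inferiority margin should not be open to that choice.

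**Working it through.** **Inputs.** From Sample size: expected T3 mean 6.0 from a baseline of 8.0 (reduction 2.0), SD 1.5, limit −1.0, true difference 0, power 80%, 56 patients required, 60 planned. From Outcomes: range 0 to 10. Assumed here: scores recorded as whole numbers; residual normality judged by Shapiro-Wilk at 5%; and, for step 3 only, an SD of change of 1.5.

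**1. The plan's own figure is on the raw scale.** Patients per arm = 2 × SD² × (z_α + z_β)² / margin². With one-sided 5%: 2 × 1.5² × (1.645 + 0.842)² / 1.0² = 27.8, so 28 per arm and 56 in total, as stated. (With one-sided 2.5%, the lower limit of a two-sided 95% interval, it is 35.3, so 36 per arm and 72. That is a separate matter.) Either way, the margin enters as a difference in NRS points.

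**2. One NRS point on a log scale.** A result one point worse than a comparator mean c is the ratio (c + 1)/c.

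| Comparator mean c | Ratio | Log units |
|---|---|---|
| 4 | 5/4 = 1.25 | 0.223 |
| 6 | 7/6 = 1.17 | 0.154 |
| 7 | 8/7 = 1.14 | 0.134 |
| 8 | 9/8 = 1.125 | 0.118 |

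No single log-scale margin matches one point. A ratio margin fixed at the expected mean of 6 (7/6) would allow 4 × 1/6 = 0.67 point at a mean of 4 and 8 × 1/6 = 1.33 points at 8. Using 1.0 literally in log units would mean a factor of 2.72, and 6 × 2.72 = 16.3 is off the scale.

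**3. Undefined values, if a plain log were used.**
- *T3 score.* P(score rounds to 0) = Φ((0.5 − 6)/1.5) = 0.00012 per patient. For at least one of 60: 1 − (1 − 0.00012)^60 = 0.7%.
- *Reduction from baseline, no offset.* P(reduction ≤ 0) = Φ(−2/1.5) = 9.1%. On whole numbers, Φ((0.5 − 2)/1.5) = 15.9%. Of 60 patients that is 5.5 to 9.5. If the SD of change runs from 1.16 to 2.12 (baseline–T3 correlation 0.7 to 0, with SD 1.5 at each visit), the continuous figure runs from 4% to 17% and the whole-number figure from 10% to 24%.

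**4. How often the rule would be triggered.** Simulated trials of 60, with residuals from a model with arm and stratum (the planned adjustment) and Shapiro-Wilk p < 0.05:
- normal scores with SD 1.5, rounded to whole numbers: about 19%;
- half responders and half non-responders, with means 5 and 7 and total SD held at 1.5: about 20 to 21%;
- half responding by 4 points and half by 0, with SD 1.0 within each half: 84 to 89%. Here the total SD is √(2² + 1²) = 2.24, well above the planned 1.5.

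The first figure depends on the model: without the stratum term, rounding alone gives about 40%. The planned model includes the stratum, so about one in five is the relevant figure.

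**The case against.** The strongest reply is that this is a general paragraph in a condensed article. The Sample size section fixes the decision in raw points, and outcome-specific handling of non-normal residuals is commonly left to a statistical analysis plan, which is not shown. That would answer a complaint about missing detail. It does not answer this one, because the published text states a rule that covers the primary outcome and conflicts with a stated limit.

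Other parts of the reply do stand, and they rule out stronger readings that a reader might infer:

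- *That a log analysis is mandatory.* The word logarithmic is in brackets and the rule is conditional, so another transformation could be chosen. Any non-linear one still leaves the raw-point scale.
- *That the patients who did best would be dropped.* T3 scores of zero are nearly absent under the stated mean and SD (step 3), and nothing in the text prescribes a log without an offset.
- *That 9–16% of patients would have undefined values.* This needs an offset-free log of a reduction score and an assumed SD of change. A lower limit above a negative number suggests that higher is better, hence a reduction score, but the article does not fix this; T3 with baseline as a covariate is equally open.
- *That the primary test becomes impossible.* Adjusted means can be back-transformed and a bootstrap interval formed in raw points. It is feasible, but it is a choice the protocol has not made.
- *That the trigger is likely.* Rates near 90% require more spread than the plan assumes. Shapiro-Wilk is named for continuous parameters in general; for residuals the text says only that normality will be evaluated, and a graphical check need not react to rounding.

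**Conclusion.** The point holds in a limited form. A stated rule that reaches the primary outcome conflicts with a stated decision limit that has meaning only in NRS points. If the rule is triggered, the transformed coefficient cannot be set against −1.0, and the remedy would be chosen after unblinded data had been seen. That rests on the text and the ratio arithmetic alone.

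The chance of being triggered is about 20% at 60 patients, assuming whole-number scores, the planned SD and Shapiro-Wilk at 5% on residuals adjusted for arm and stratum. It rises if the outcome is more bimodal and more variable than planned. The documents do not support saying that the primary test will fail or that patients will be excluded. Because the rule is conditional and easily repaired, this is a correction that should be made, not a fatal flaw.

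**What to change.** Exempt the primary outcome from the transformation rule, for example: *The primary NRS outcome is analysed untransformed by linear regression adjusted for the stratification factor. If residuals are non-normal, the confidence interval for the mean difference in NRS points uses heteroscedasticity-robust (HC3) standard errors or a stratified bootstrap, and is compared with the same −1.0 margin.* Choose one of the two methods in advance, so that this too is not decided on the data.

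Keep transformations for positive, skewed secondary measures such as sIL-2R.

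The cost is one sentence in a protocol amendment or the statistical analysis plan, written before the primary data are analysed. The sample size calculation is already in raw points and does not change because of it.
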